### Diagnostic criteria for traditional Chinese medicine patterns

According to the 2002 Guidelines for Clinical Research of Chinese Medicine (new drug), any patient presenting with the primary symptoms mentioned below and at least one of the secondary symptoms, with typical tongue and pulse presentations, will be diagnosed with qi deficiency and blood stasis syndrome. Primary symptoms include chest pain and chest tightness. Secondary symptoms include shortness of breath, fatigue, palpitations and/or spontaneous perspiration. .

#### *Inclusion criteria*

1. Patients ages 40 to 75 years old

2. Provision of signed informed consent

3. Diagnosis of angina pectoris due to CHD (stable angina, New York Heart Association (NYHA) classes I to III)

4. TCM pattern diagnosis of qi deficiency and blood stasis

#### *Exclusion criteria*

1. Patients younger than 40 or older than 75 years old

2. Diagnosis of NYHA class IV CHD

3. Uncontrolled NYHA class III hypertension (systolic blood pressure ≥180 mmHg and/or diastolic blood pressure ≥110 mmHg)

4. Presence of severe arrhythmia

5. Patients with serious primary hepatic, renal, hematologic or mental illness and those with malignant tumors

6. Presence of active peptic ulcers and other hemorrhagic diseases

7. Pregnancy or lactation

8. Patients with other complications who should not be included in the trial as adjudged by the recruiting personnel

9. Patients with an allergic constitution or a history of allergy to the investigational drug

10. Participation in another clinical trial, either currently or within the past 3 months

#### *Exclusion criteria*

1. Incidence of serious adverse events.

2. Major design flaws or serious deviation from research protocol

3. Cancellation of the study by administrative authorities

### Patient grouping and treatment allocation

Using stratified and blocked randomization, we will first categorize eligible participants into four groups on the basis of their varied choice of secondary symptoms to be addressed, and then we will randomly assign them to one of the two treatment arms at a ratio of 1:1. To minimize imbalances across groups, gender will also be used as a stratification factor. The random number sequence will be generated by a third-party statistician using SAS version 9.1 software (SAS Institute, Cary, NC, USA).

The four symptom combination groups, each representing the signs a patient most wishes to bring under control, were formed according to the characteristic physical manifestations of the qi deficiency and blood stasis syndrome defined in the 2002 Guidelines for Clinical Research of Chinese Medicine (new drug). The grouping criteria for patients with varying therapeutic needs resulted in the following four symptom combination groups:

1. Combination 1: chest pain + chest tightness + shortness of breath

2. Combination 2: chest pain + chest tightness + fatigue

3. Combination 3: chest pain + chest tightness + palpitations

4. Combination 4: chest pain + chest tightness + spontaneous perspiration

### Sample size calculation

Sample size estimation is based on the results of a pilot study that showed the difference in changes in Seattle Angina Questionnaire (SAQ) scores of 2 ± 2.5 between the group receiving QSYQ dripping pills and the group taking TXL capsules. Assuming a two-sided *P*-value of 0.05, 90% power and calculating for a dropout rate of 20%, one would need to have approximately 160 patients with 80 in each treatment group. We used the PAST software program to calculate these statistics (http://folk.uio.no/ohammer/past/) [10]. Therefore, we plan to recruit 40 patients for each of the four symptom combinations, from among whom 20 will be assigned to treatment arm A (QSYQ) and 20 to treatment arm B (TXL). In all, 160 patients will be recruited.

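### The stated sample-size inputs do not give 80 per group and 160 in total: with 2.5 read as the SD of change they give 42-43 per group (84-86 in total)

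*Protocol article*

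**What the plan says.** The Sample size calculation section of the protocol article bases the number on a pilot study with a "difference in changes in Seattle Angina Questionnaire (SAQ) scores of 2 ± 2.5" between the two drug groups. It does not say what the 2.5 is. The other inputs are a two-sided 0.05 level, "90% power and calculating for a dropout rate of 20"%. From these it concludes that "one would need to have approximately 160 patients with 80 in each treatment group". The allocation section says that patients are randomised so as to "randomly assign them to one of the two treatment arms at a ratio of 1:1".

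The next sentence of the sample-size section opens with *Therefore* and plans 40 patients for each of four symptom combinations, 20 per arm, 160 in all.

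The Study design and Assignment of interventions sections describe a crossover: 4 weeks on one treatment, a 10-day washout, then 4 weeks on the other. Every patient is to receive both treatments.

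**The concern.** All the inputs of a standard two-group calculation are on the page, so the output can be checked, and it is roughly twice what the inputs give. A planning figure and its power statement are what a reader uses to judge whether the trial is the right size. Here the 90% does not belong to the 160 on the natural reading of the inputs.

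Two further mismatches sit in the same paragraph. The calculation speaks of two treatment groups, although the treatments are compared within patients. And *Therefore* presents the 40 per symptom combination as following from a power calculation that has no symptom combination in it.

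**Working it through.** **Inputs** (Sample size calculation; 1:1 ratio from Patient grouping and treatment allocation): difference 2; SD 2.5 (assumption: 2.5 is the SD of the SAQ change); two-sided alpha 0.05; power 90%; dropout 20%.

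**1. Attempt to reproduce 80 per group.**

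n per group = 2 × (1.960 + 1.282)² × (2.5/2)² = 2 × 10.51 × 1.5625 = 32.8, so 33. The t-test version gives 33.8, so 34.

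Dropout by division: 33/0.8 = 41.25, so 42; 34/0.8 = 42.5, so 43. Total 84-86.

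Stated total over computed total: 160/86 = 1.86 to 160/84 = 1.90. The figure is not reproduced.

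**2. Variants, per group after division by 0.8.**

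| Variant | Per group |
|---|---|
| One-sided 0.05, 90% power | 34-35 |
| Two-sided, 95% power | 52-53 |
| Two-sided, 99% power | 73-74 |
| Bonferroni over four combinations, 90% power | 57 |
| Rank test (efficiency 0.955 or 0.864), 90% power | 44-50 |

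None gives 80.

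**3. What 80 per group delivers.** After 20% dropout, 80 × 0.8 = 64 evaluable per group. With a standardised difference of 2/2.5 = 0.8, power is 99.4% (t-test) to 99.5% (normal).

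**4. What would make 90% true at 64 per group.** The detectable standardised difference at 90% power is 0.577 (t-test).

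- With SD 2.5, the difference would be 0.577 × 2.5 = 1.44 points (normal approximation 1.43).
- With a difference of 2, the SD would be 2/0.577 = 3.46 (normal approximation 3.49).

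**5. The same inputs on a within-patient basis** (paired t-test, total patients).

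- If 2.5 is the SD of the within-patient difference: 18.4, so 19; 19/0.8 = 23.75, so 24.
- If 2.5 is the SD in each period and the within-patient correlation is assumed to be zero, the SD of the difference is 2.5 × √2 = 3.54: 35; 35/0.8 = 43.75, so 44.

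The document gives no within-patient SD or correlation, so these show only that a crossover calculation does not lead to 160 either.

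**The case against.** The strongest reply is that ± 2.5 is undefined. It could be the SD of change, the SD of a single score, the SD of the within-patient difference, or a standard error. One reading comes close to the stated figure. If 2.5 is the SD of one score and a change is the difference of two uncorrelated scores, the SD of change is 2.5 × √2 = 3.54. Then n = 2 × 10.51 × (3.54/2)² = 65.7, so 66, and 66 × 1.2 = 79.2, so 80 per group. On that reading 64 evaluable per group have about 89% power and 160 is about right. This stands as a possibility. It does not clear the paragraph: the text attaches 2.5 to the difference in changes, the conversion is unstated, and allowing for 20% loss by division gives 66/0.8 = 82.5, so 83 (84 with the t-test). The fault would then be an unlabelled SD rather than a twofold excess.

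A reader might infer that 80 is the total for both groups printed as the size of each, since 33 × 1.2 = 39.6, so 40 per group. The documents do not show this, and the √2 route fits the printed number equally well. The cause is unknown.

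A reader might also infer that the trial is underpowered within a symptom combination. The sample-size section claims 90% only for two treatment groups, never for a combination. The planned analysis classifies each patient against an MCID and applies correspondence analysis, with no t-test within a combination, and the Discussion calls the study exploratory. Power figures for such a test would describe an analysis that is not planned.

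Finally, the error is towards more patients than the inputs require, and so is ignoring the crossover. That limits the consequence to the reporting of the sample size.

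**Conclusion.** The sample-size statement is wrong as written. Taking 2.5 as the SD of the SAQ change, the inputs give 42-43 per group and 84-86 in total, against the stated 80 and 160, and the stated number carries about 99% power rather than 90%. The word *approximately* does not cover a factor of 1.9.

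The size of the gap rests on that reading of 2.5. Under the √2 reading the number is nearly right, but the SD used is not the one printed. Under the standard-error reading nothing can be checked without the pilot's size. On the reading checked, the printed inputs and the printed output disagree, so this is not detail lost in condensing an article.

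Independently of what 2.5 means, the calculation is framed for parallel groups in a crossover trial, and it gives no support for 40 per symptom combination as a derived figure. The documents do not show that the overall comparison is underpowered.

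**What to change.** Rewrite the Sample size calculation paragraph:

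1. State what 2.5 is (SD of change, SD of one score, SD of the within-patient difference, or standard error), and correct it if it is not the SD that was used.
2. Name the comparison that was powered and base it on the crossover, giving the within-patient SD or the correlation assumed.
3. Restate either the required number (84-86 as parallel groups if the SD is 2.5) or the power that 160 delivers (about 99% as parallel groups if the SD is 2.5).
4. If 160 was chosen to give 40 per symptom combination, say so directly, and do not present it as the result of the 90% power calculation.

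The cost is one paragraph and a look back at the pilot data. Planned enrolment can stay at 160.

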### Randomization

Randomization of the trial participants will be completed using an independent data center using an interactive voice response system.

#### *Blinding and allocation concealment*

The test drug will be coded and placed in indistinguishable containers by specially assigned personnel who will not participate in other procedures in the trial. Drug assignments will be enclosed in sealed, opaque envelopes and kept confidential by the trial management board. Thus, the patients, clinicians, participating nurses, trial coordinators, outcome assessors and statisticians will be blinded to treatment assignment.

#### *Baseline assessment*

General information about the patient’s gender, age and heart function will be collected and assessed after eligibility screening to ensure balanced baseline values.

#### *Assignment of interventions*

In this study, we adopt a crossover design which involves three key phases: a 4-week treatment period, a 10-day washout period and the crossover of treatment for another 4 weeks:

1. The first treatment period (4 weeks): A total of 160 participants will be randomly assigned to receive treatment A or treatment B for 4 weeks.

1.a. Treatment A: QSYQ dripping pills + TXL placebo + routine medication

1.b. Treatment B: TXL capsules + QSYQ placebo + routine medication

2. Washout phase (10 days): After the first round of treatment, patients in both groups will receive QSYQ placebo and TXL placebo plus routine medication for 10 days.

3. Crossover of treatments (4 weeks): In this stage, patients formerly assigned to treatment A will be switched to treatment B and those assigned to treatment B will be switched to treatment A.

#### *Routine medication*

Routine medications will include aspirin, angiotensin-converting enzyme inhibitors or angiotensin receptor blockers, β-receptor blockers, statins and nitrates.

#### *Concomitant medications*

1. Dihydropyridines and diuretics

2. Antidiabetic drugs

3. Digoxin and diuretics

### Measurement tools and time of data capture

The SAQ and 15-point Likert scale scores will be used to collect PROs immediately following the first treatment period and the crossover treatment period. The minimal clinically important differences (MCIDs) of the SAQ and the Likert scale scores at these two time points will be calculated for efficacy evaluation and comparison.

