## Objectives

We are conducting a multicenter, randomized, controlled, double-blind, double-dummy clinical trial to compare the effectiveness of two Chinese patent medicines for angina patients diagnosed with qi deficiency and blood stasis syndrome. The ultimate goal is to test the proposed methodology for the individualized evaluation of the therapeutic effects of Chinese patent drugs and for distinguishing between drugs targeting a multitude of similar indications.

To fulfill these objectives in our present study, we highlight the introduction of trial participants’ therapeutic needs and willingness in terms of group allocation and the use of CER methodology. Specifically before being entered into the randomization process, all eligible participants with qi deficiency and blood stasis syndrome will first be allowed to choose from among four prespecified groups of symptoms which they would most like to be addressed. The outcomes for these symptoms are considered PIOs and will be assessed using PRO instruments. Furthermore, we will test the use of the CER method to compare the curative effects of QSYQ dripping pills and TXL capsules, two widely used Chinese patent medicines for angina patients with qi deficiency and blood stasis syndrome. By analyzing and comparing the effects of the two drugs for each symptom group, we aim to summarize the characteristics of the drugs’ curative effects and identify the best targeted indications for each drug.

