**Figure 2 F2:**
[figure not shown]
**Calculation of the M value.** SAQ, Seattle Assessment Questionnaire.

1.a.i. Find patients receiving treatment A (or treatment B) whose self-reported Likert scores are within the range of +2 to +3.

1.a.ii. Collect the corresponding SAQ score of these patients, use X_1_ to refer to it and calculate the mean value $X{\left(—\right)}_{1}$.

1.a.iii. Find patients receiving Treatment A (or Treatment B) whose self-reported Likert scores are within the range of 0 to +1.

1.a.iv. Collect the SAQ scores of these patients, use X_0_ to refer to it and calculate the mean value X_0_

1.a.v. $M_{0}=X_{0}-X{\left(—\right)}_{0}$

1.a.vi. $M_{1}=X_{1}-X{\left(—\right)}_{1}$

2. Calculation of SEM (SEM_0_ and SEM_1_) [7,12,13].

$$\mathrm{SEMO}=\sqrt{\sum M0^{2}/\left(n-1\right)}\times \sqrt{1-r}$$

$$\mathrm{SEM}1=\sqrt{\sum M1^{2}/\left(n-1\right)}\times \sqrt{1-r}$$

n:sample size; r:the reliability coefficient of SAQ

3. Calculation of MCID We will calculate the MCIDs for treatment A (referred to as MCID1) and treatment B (referred to as MCID2) during the first treatment period and for treatment A (referred to as MCID3) and treatment B (referred to as MCID4) during the crossover period.

MCID, Minimal clinically important difference; SEM, Standard error of measurement.

$$\mathrm{MCID}\;=\;\sqrt{\mathrm{SEM}O^{2}+\mathrm{SEM}1^{2}}$$

4. Individualized efficacy evaluation upon the first round of treatment: Treatment interventions will be defined as either effective or ineffective by comparison of the patient’s personal SAQ score with the calculated MCID value.

4.a. Treatment A will be defined as effective if a patient receiving it has a SAQ score greater than the MCID1 score.

4.b. Treatment B will be defined as effective if a patient receiving it has a SAQ score greater than the MCID2 score.

4.c. A treatment will be adjudged ineffective if a patient receiving it reports a SAQ score lower than the corresponding MCID value (MCID1 or MCID2).

5. Individualized efficacy evaluation upon crossover of treatment: Because of the complexity of the study design, all the patients will be categorized into four groups by using the following assessment tools:

5.a. Group 1: Both treatments A and B are effective for patients in this group:

5.a.i. For patients who first receive treatment A and then treatment B, the first SAQ score > MCID1 and the second SAQ score > MCID4

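### The comparison the trial is sized on is never tested or named as primary, and the efficacy readings that replace it are unranked

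*Protocol article*

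**What the plan says.** **Sample size calculation.** The trial is sized on a pilot result for one quantity, "the difference in changes in Seattle Angina Questionnaire (SAQ) scores of 2 ± 2.5", between the two drug groups. The design values are "Assuming a two-sided *P*-value of 0.05, 90% power", with 20% dropout, giving 160 patients (80 per group).

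**Objectives.** The purpose is wider: "By analyzing and comparing the effects of the two drugs for each symptom group", the authors aim to identify the best-targeted indications of each drug.

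**Measurement tools and time of data capture.** SAQ and the 15-point Likert scale are collected after the first treatment period and after the crossover period. The section then says: "The minimal clinically important differences (MCIDs) of the SAQ and the Likert scale scores at these two time points will be calculated for efficacy evaluation".

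**Efficacy assessment tools.** The Likert score appears only as a selector, as in "Find patients receiving treatment A (or treatment B) whose self-reported Likert scores are within the range of +2 to +3"; the SAQ scores of those patients enter the calculation. The coefficient r is the reliability of the SAQ, and MCID1 to MCID4 are thresholds for SAQ scores. Step 4 gives a first-period reading: "Individualized efficacy evaluation upon the first round of treatment: Treatment interventions will be defined as either effective or ineffective". Step 5 sorts patients into four groups after the crossover.

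**Statistical analysis and Correspondence analysis.** Significance tests are named for baseline balance and, under Safety, for adverse events. Tables 1 and 2 tabulate the step 5 groups by symptom combination. The best indication is read from the nearest pair of points in the biplot.

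**The concern.** A significance level and a power belong to one stated comparison. Here they are attached to a between-drug difference in SAQ change, which the analysis sections then leave out. What they contain is a set of classifications and a graphical rule, with nothing saying which of these decides between the drugs.

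Two things are at stake. First, the comparison for which 160 patients are recruited has no planned test, so the 90% power claim does not carry over to any reported result. Second, a drug's best indication can be named from whichever reading stands out, and readers may take the 0.05 in the sample size section as covering that claim. The mention of a Likert MCID adds doubt about whether Likert is an efficacy outcome in its own right.

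**Working it through.** **1. What the sized comparison requires.** Inputs, all from Sample size calculation: difference 2; SD 2.5 (reading the ± figure as an SD, which is an assumption); two-sided 0.05; power 90%; dropout 20%.

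- Per group: n = 2 × (1.960 + 1.282)² × 2.5² / 2² = 2 × 10.51 × 1.5625 = 32.8, so 33.
- With dropout: 33 / 0.8 = 41.25, so 42 per group and 84 in all. Inflating by 33 × 1.2 gives 40 per group and 80 in all.

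The stated 80 per group and 160 in all are not reproduced. That is a separate matter. For this point it shows that the numbers are ample for the sized comparison: with 80 × 0.8 = 64 completers per group, 2 / (2.5 × √(2/64)) = 4.53, and Φ(4.53 − 1.96) gives a power of 99.5%. What is missing is the test itself.

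**2. Is that comparison analysed?**

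| Place | What is analysed | Tests the QSYQ–TXL difference in SAQ change? |
|---|---|---|
| Test for baseline balance | baseline variables | no |
| Step 4 | each patient's SAQ score against MCID1 or MCID2 | no |
| Step 5, Tables 1 and 2 | counts in four outcome groups | no |
| Correspondence analysis | distances in a biplot | no |
| Safety | adverse event incidence, χ² | no |

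**3. What the nearest-distance rule provides.** It is prespecified and rests on step 5 only, through Tables 1 and 2. In any plot some pair of points is nearest, whether or not symptom combination and outcome are associated. The rule therefore always returns an answer and has no stated error rate.

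**4. The Likert role.** The data-capture section speaks of an MCID for the Likert score. The calculation steps use Likert to pick patients, SAQ scores as the data and SAQ reliability as r. Every rule in steps 4 and 5 compares a SAQ score with a threshold. No step defines a Likert MCID, so the two places need reconciling.

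**5. Step 5 as a drug contrast.** For patients given B (TXL) first, step 5.b.ii places a first score above MCID2 and a second below MCID3 in Group 2, described as A effective and B ineffective. Step 4.b calls a score above MCID2 evidence that B is effective. Step 5.c.ii is reversed in the same way. As printed, Group 2 means that the first period was effective and the second was not, whichever drug came first. Suppose response rates of 60% on A and 50% on B, equal sequences and no period effect:

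- A-first: Group 2 minus Group 3 = 60 − 50 = +10 points.
- B-first: 50 − 60 = −10 points.
- Average: 0, where the drugs differ by 10 points.

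**6. Illustration of unranked readings.** Take six SAQ contrasts: first period, crossover overall, and crossover in each of the four symptom groups. Assume each is read at two-sided 0.05, which the plan does not state. If independent, the chance of at least one false difference is 1 − 0.95⁶ = 0.265. The contrasts overlap, so I simulated identical drugs with 160 patients, 50% response and step 5 labelled correctly. The result is about 0.22 (0.20 to 0.23 for within-patient correlations of 0.3 to 0.7).

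**The case against.** **The study is exploratory and has a reading rule.** The Discussion calls it exploratory, and the Correspondence analysis section prespecifies how an indication is found. Both are true, and they soften the consequence. They do not say which reading decides between the drugs, and they sit beside a claim of 90% power at two-sided 0.05 and a goal of finding where each drug is most effective.

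**Hierarchy and alpha allocation belong in an analysis plan.** For the details, yes. The point rests on what the article does state: it sizes for one comparison and then sets out an efficacy analysis that omits it. Naming the deciding comparison is a protocol matter.

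**There is no efficacy test, so there is no false-positive rate.** This stands. A reader might infer that 0.22 is the error rate of this plan. It is not, because it needs tests that the plan does not contain.

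**Likert is not a second outcome.** This also stands. A reader might infer from the data-capture section that every SAQ reading is repeated on Likert, doubling the number of contrasts. No step defines a Likert verdict, and Tables 1 and 2 use none, so those contrasts should not be counted.

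**Step 4 is not a rival drug comparison.** It classifies individual patients; no passage compares its rates between arms, and step 5 reuses its scores and thresholds. A reader might infer that steps 4 and 5 will often favour different drugs. In simulations with 64 completers per sequence, opposite signs occur in 20–26% of trials when the drugs are identical, where direction carries no information, and in 9–11% at 60% versus 50%. This is a reason to rank the two steps, not evidence that they routinely conflict.

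**Conclusion.** The point holds in this form: the comparison that justifies the sample size is neither named as primary nor tested. The readings used in its place are unranked and without error control. The Likert MCID in the data-capture section conflicts with the SAQ-only calculation steps.

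This conclusion comes from setting the sections side by side and needs no simulation. The 0.22 against 0.05 is an illustration that depends on reading six SAQ contrasts at 0.05 each. The loss of a 10-point difference to 0 in step 5 depends on the printed labels, equal sequences and no period effect. The documents do not support the claim that the plan has a particular inflated error rate, or that Likert supplies a second set of verdicts. The sponsor should correct this; it does not by itself invalidate the design.

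**What to change.** 1. In Measurement tools and time of data capture, state that the Likert score serves only as the anchor for the SAQ MCID, and delete the reference to a Likert MCID.
2. Name the sized comparison as the single primary contrast: the within-patient QSYQ-minus-TXL difference in SAQ score over both periods, all symptom groups together, with period and sequence in the model, at two-sided 0.05. Use change where a pre-period score is available; the sample size speaks of changes, while the data-capture section lists only the two post-treatment points.
3. Label step 4, the symptom-group comparisons and any best indication drawn from the correspondence analysis as secondary and hypothesis-generating.
4. Before step 5 is used for any drug contrast, reconcile the labels in 5.b.ii and 5.c.ii with step 4.b for the B-first sequence.

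The cost is a few sentences, with no added patients. The downside is that symptom-group findings, which the Objectives emphasise, can no longer be presented as confirmed.
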